**Secondary outcomes: patient-reported outcomes**										
	Quality of life: the EQ-5D-5L^f^ is a standardized instrument used to measure health-related quality of life in a wide range of health conditions and treatment settings [27].	✓		✓		✓				✓
	Knowledge: an 8-item curriculum-based measure was purpose designed to assess knowledge about four key topics of dialysis self-management covered in the SUCCESS^g^ app: (1) diet, (2) fluids, (3) medicines, and (4) physical activity. Questions (two per topic) were based on key learnings from the app, with points scored for correct answers (0 = incorrect, 1 = correct).	✓		✓		✓				✓
	Health behavior**:** a theory-informed 11-item behavior questionnaire was adapted from previous literature [28] and matched to the content of the SUCCESS app. Participants are asked to respond “yes” or “no” to engaging in behaviors over the past week, such as “Checking the nutrition label when eating packaged food” (0 = no, 1 = yes).	✓		✓		✓				✓
	Confidence: an 11-item confidence measure was purpose designed based on the health behavior questionnaire above, including questions such as “How confident do you feel reading and understanding food labels?” Items are rated on a 5-point ordinal scale ranging from 1 (“not at all confident”) to 5 (“extremely confident”).	✓		✓		✓				✓
	Self-management: two questions were designed to assess patient knowledge and adherence to phosphate binder medication prescription, as an indicator of self-management.	✓		✓		✓				✓
**Secondary outcomes: clinical outcomes**										
	Changes in symptom burden: the POS^h^ is a widely used and validated instrument used in clinical care and research. The POS-Renal is a short measure (11 questions) that collects information on the most common symptoms that renal patients experience [29].	✓		✓		✓				✓
	Nutritional status: the PG-SGA^i^ is a standard nutritional assessment tool measuring clinical indices (ie, weight, intake, symptoms, functional status, disease state, metabolic stress, and nutritional physical examination) in a range of chronic conditions [30]. The PG-SGA enables the patient and professional to quickly and easily assess and monitor the risk for malnutrition and to evaluate effects of interventions.	✓		✓		✓				✓
	Interdialytic weight gain: this is a measure of weight gained between two consecutive dialysis sessions. The measure gives an indication of whether patients are adhering to fluid restrictions and is recorded at each dialysis session; the monthly average is easily calculated for each patient.	✓		✓		✓				✓
	Key performance indicators: typical key performance indicators for dialysis will be linked and extracted from the Australian and New Zealand Dialysis and Transplant registry. This will include demographics, ethnicity, anthropometry, comorbidities, course of treatment, and survival rates.	✓		✓		✓				✓
	App analytics—the following information will be extracted using Google Analytics: How many people have registered or logged in? How often do people log in? At what times? How does this relate to their dialysis times? How long do people stay logged in? Time between visits Number of times people access app features (eg, quizzes and videos) Number of visits to each page and subpage.	✓		✓		✓				✓

^a^A checkmark indicates that the measure will be performed at the indicated timepoint.

^b^MoCA: Montreal Cognitive Assessment.

^c^MMSE: Mini–Mental State Examination.

^d^MACL: Multicomponent Assessment of Computer Literacy.

^e^HLQ: Health Literacy Questionnaire.

^f^EQ-5D-5L: 5-level EQ-5D.

^g^SUCCESS: Supporting Culturally and Linguistically Diverse CKD Patients to Engage in Shared Decision-Making Successfully.

^h^POS: Palliative care Outcome Scale.

^i^PG-SGA: Patient-Generated Subjective Global Assessment.

### Data Collection and Management

Quantitative data will be either collected using paper copies or captured electronically via REDCap, a web-based tool to capture data for clinical research and to create databases and projects. Baseline data will be collected in person, and follow-up data will be collected either in person or electronically based on patient preference and depending on COVID-19 restrictions at the time of data collection.

After enrollment, a unique identifier will be assigned to each study participant. Personal information about participants will be kept separate from the main data set and will not be shared. All data will be stored on password-protected REDCap databases. Spreadsheets and data analysis derived from this data will be stored in the University of Sydney Research Data Store only, and will not be downloaded to individually owned computers.

### Qualitative Substudy

Qualitative data will be collected from participants at 3, 6, and 12 months. Semistructured interviews will be conducted by research staff trained in qualitative methods, in order to explore the experiences and perspectives of individual participants regarding usage of the app. The perspectives of users on the applicability of content and their ability to build capacity, become motivated, and identify opportunities to improve the management of their CKD will also be sought. Additional feedback from research participants on the content and design of the app will be discussed.

Participants for qualitative interviews will be purposively selected from those already enrolled to capture a range of demographic characteristics, including those with lower health literacy and from culturally and linguistically diverse backgrounds. Interviews will be conducted face-to-face during participants’ scheduled dialysis sessions or virtually via approved videoconferencing software. Participants dialyzing at home may complete interviews over the phone or virtually or can arrange a time to meet the interviewer at the dialysis clinic, depending on the COVID-19 restrictions at the time. All participants will have provided consent to participate in the interviews at the beginning of the study. Verbal consent will be confirmed for the interview, and the audio recording will be obtained at the start of the interview. The semistructured interviews are expected to last between 20 and 60 minutes and will be audio recorded.

### Data Analysis

#### Overview

Analysis of data will occur using an intention-to-treat approach and will compare the intervention and usual care arms. For continuous and binary outcomes, linear and logistic regression models will be used, respectively, with study arm as a covariate. All models will also be adjusted for center using a random effect, and the type of patient (ie, receiving home-based or in-center care) will be adjusted for using a covariate.

Qualitative data will be analyzed using the Framework approach to thematic analysis [31]. Framework analysis is a matrix-based approach with columns depicting themes and rows listing the cases, enabling the relationship between themes and cases to be explored. The first step involves familiarization with the data, where one or two researchers will review the transcript and, using an inductive approach, they will then develop a list of emerging topics and salient themes. These initial impressions will form the basis of the coding framework. Then, additional researchers will independently read a subset of transcripts and review the framework, which will further be revised with continuous discussion if needed. One researcher will then code all the interviews into the final framework, of which a random subset (10%) will be double coded by an additional researcher to ensure rigor. Similarities or differences will be discussed and reassessed. Microsoft Excel will be used to summarize the themes and supporting quotes from each transcript in the framework. Prominent themes arising from the framework will be identified and discussed in-depth with the research team.

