### Design

The SUCCESS trial is a 12-month multicenter pragmatic RCT with a 1:1 allocation to two groups: SUCCESS app plus usual care versus usual care alone.

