### Timeline

The study timeline will include four data collection timepoints: baseline and 3-month, 6-month, and 12-month follow-ups (Figure 1).

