### Study Outcomes

Once informed consent is obtained, baseline measures will be collected, including demographics, dialysis history, cognition level, and health and digital literacy status (Table 1 [20-30]). Our primary outcomes are health literacy, shared decision-making, and rates of unscheduled health encounters; these will be assessed at 3, 6, and 12 months of app usage (Table 1). Secondary outcomes include patient-reported outcomes and clinical outcomes; these will also be assessed at 3, 6, and 12 months of app usage (Table 1).

**Table 1 table1:** Measurements collected throughout the trial.

Measure and description			Timepoint (month)							
			0		3		6		12	

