### Sample Size

Our sample size has been calculated based on the primary outcome of the three Health Literacy Questionnaire (HLQ) domains. We assumed a minimal clinically important difference of 0.25 units in any one of the three HLQ domains. A sample size of 384 participants would result in greater than 90% power to detect a 0.25-unit change in an HLQ domain between the two arms, assuming an SD of 0.60, and at least 80% power, assuming an SD of 0.75. These SD values are based on published literature and equate to a standardized difference of 0.42 and 0.33, respectively; a standardized difference of 0.5 is considered a medium effect [33,34]. Our power calculation is based on conducting our analyses using 2-sided tests, a 5% significance level, and assuming 20% loss to follow-up (eg, due to death or kidney transplant).

For qualitative interviews, a maximum total sample size of 40 participants is planned. Interviews will continue until data saturation or until the maximum total sample size is reached.

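### The adjustment set for the outcome models omits the month-0 value of the outcome, giving up precision and protection against chance baseline imbalance

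*Protocol article*

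**What the plan says.** The Data Analysis Overview sets out the quantitative models in two sentences. For continuous and binary outcomes, "linear and logistic regression models will be used, respectively, with study arm as a covariate". The next sentence extends the set: "All models will also be adjusted for center using a random effect", and home-based versus in-center care enters as a covariate. No other adjustment variable is named there.

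Study Outcomes states that "Once informed consent is obtained, baseline measures will be collected", and Timeline lists "four data collection timepoints: baseline and 3-month, 6-month, and 12-month follow-ups". Table 1 marks the three HLQ domains and the Decision Self-Efficacy Scale at month 0 and at every follow-up, and does the same for the secondary outcomes. The third primary outcome, unscheduled health encounters, is marked at months 3, 6 and 12 only.

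The Missing Data section uses possession of baseline data as a condition for staying in the outcome analysis. It does not say how those data enter a model.

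**The concern.** For a score measured before and after allocation, the baseline score is usually the strongest available predictor of the follow-up score. Leaving it out puts variance that could have been explained into the residual, so the treatment effect is estimated less precisely than the collected data allow.

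There is also the matter of chance imbalance. In-center patients are allocated by attendance pattern within center, so that part of the trial has few allocation units. A chance difference between arms in baseline HLQ would carry over into follow-up, and the listed terms would not correct for it.

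The plan is also not fully coherent: participants can be dropped for lacking a value that the listed model does not use.

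**Working it through.** **Inputs from the protocol article.** Sample Size gives N = 384, a difference of 0.25 HLQ units, SDs of 0.60 and 0.75, and "2-sided tests, a 5% significance level, and assuming 20% loss to follow-up". Design gives "with a 1:1 allocation to two groups". Study Setting names six hospitals and six community centers, so at most 12 × 2 = 24 day-pattern clusters. Results reports nine sites recruiting, about 18 clusters.

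**Assumed, because not given.** Baseline to follow-up correlation r from 0.3 to 0.7; intracluster correlation (ICC) of 0.02 and 0.05.

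**Step 1: reproduce the stated power.** Analyzed per arm: 384 × 0.8 / 2 = 153.6 (307.2 in total). SE = SD × √(2/153.6); power = Φ(0.25/SE − 1.960).

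- SD 0.60: SE = 0.0685, 0.25/SE = 3.651, power = Φ(1.691) = 95.5%.
- SD 0.75: SE = 0.0856, 0.25/SE = 2.921, power = Φ(0.961) = 83.2%.

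The plan says "A sample size of 384 participants would result in greater than 90% power to detect a 0.25-unit change in an HLQ domain", "assuming an SD of 0.60, and at least 80% power, assuming an SD of 0.75". Both bounds hold without any baseline adjustment. The exact t-test gives 82.9% instead of 83.2%.

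**Step 2: add the baseline value.** The SD becomes SD × √(1 − r²). The last column is the total N for 80% power at SD 0.75: twice the per-arm n, divided by 0.8 for loss.

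| r | variance factor 1 − r² | power, SD 0.60 | power, SD 0.75 | total N |
|---|---|---|---|---|
| 0 (as listed) | 1.00 | 95.5% | 83.2% | 355 |
| 0.3 | 0.91 | 96.9% | 86.5% | 323 |
| 0.5 | 0.75 | 98.8% | 92.1% | 265 |
| 0.7 | 0.51 | 99.9% | 98.3% | 183 |

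**Step 3: allow for clustering.** This is an upper bound: all patients in-center, equal clusters, no credit for pairing day patterns within center, and the ICC unchanged by adjustment. Design effect DE = 1 + (307.2/k − 1) × ICC for k clusters. Power at SD 0.75:

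| clusters | ICC | DE | unadjusted | r = 0.5 | r = 0.7 |
|---|---|---|---|---|---|
| 24 | 0.02 | 1.24 | 74.8% | 85.9% | 95.7% |
| 24 | 0.05 | 1.59 | 63.9% | 76.3% | 90.0% |
| 18 | 0.02 | 1.32 | 71.9% | 83.5% | 94.5% |
| 18 | 0.05 | 1.80 | 58.5% | 70.9% | 86.1% |

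Adjustment fully offsets clustering only if (1 − r²) × DE < 1, that is, r > √(1 − 1/DE). For DE 1.24 this needs r above about 0.44; for DE 1.59, above about 0.61.

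**Step 4: size of chance imbalance.** The SD of the baseline difference between arms, in SD units, is √(4 × DE/307.2). It is 0.114 under individual randomization, 0.127 and 0.144 with 24 clusters (ICC 0.02 and 0.05), and 0.131 and 0.153 with 18. An imbalance d shifts the expected follow-up difference by about r × d. At r = 0.5 and d = 0.127 the shift is 0.064 SD, against a planned effect of 0.25/0.75 = 0.333 SD: 0.064/0.333 is about 19%.

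**The case against.** The strongest reply is that two sentences in a journal article are a summary. They do not say the covariate list is exhaustive, and they do not say how the three follow-up times are handled. A baseline covariate could well appear in the full analysis plan. Some wording hints at it: the baseline requirement under Missing Data, the power statement in terms of a change, and symptom burden labelled as a change outcome.

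Part of this stands. A reader might infer that the trial will compare raw follow-up scores; the article does not say so, and that should not be asserted. But the article does more than stay silent. It names an adjustment set and applies it to all models, and someone following it would leave baseline out. The hints do not say how baseline enters.

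The second reply is that the imbalance argument is limited, and this stands too. Home patients are randomized individually. Each center places its two day patterns in opposite arms, so differences between centers largely balance. Even ignoring that pairing, the SD of the chance baseline difference with 24 clusters rises only from 0.114 to 0.127–0.144.

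The third reply is that the benefit rests on an r and an ICC that the article does not supply. That is correct, which is why ranges are shown.

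**Conclusion.** The point holds as a matter of efficiency and robustness. The listed adjustment set omits a covariate already collected for two of the three primary outcomes and nearly all secondary ones. Under the independent-patient formula with r between 0.3 and 0.7, including it removes 9% to 49% of residual variance and lifts power at SD 0.75 from about 83% to 86%–98%.

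Three stronger readings are not supported. A reader might infer that the comparison is biased; leaving out a baseline covariate does not by itself bias a randomized comparison. A reader might infer that the stated power is wrong; it reproduces without the covariate. A reader might infer that adjustment would pay for clustering and multiplicity together. In the upper-bound clustering case with 24 clusters, ICC 0.05 and r = 0.5, adjusted power is still only 76.3%, and no offset for multiplicity has been shown.

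This should be changed, but nothing in the trial's validity depends on it.

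**What to change.** Add to Data Analysis, Overview: *Each model for an outcome measured at month 0 includes the baseline value of that outcome as a covariate.* Unscheduled encounters fall outside this sentence because Table 1 records no month-0 value for them.

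If participants with a missing baseline value are to be kept, by a constrained longitudinal model or by mean imputation of the covariate, amend the exclusion rule under Missing Data to match. As written it would remove them.

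Make the change before outcome data are compared by arm, so that the adjustment cannot look chosen after the fact. The cost is one degree of freedom per model and no new data.

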#### Missing Data

We will use best practice to decide when imputation is necessary for missing data, except for the outcome data, considering the percentage of missing data and plausibility of the “missing at random” assumption [32]. Where there is a large proportion of missing data, we will consider using a complete case or pairwise deletion approach. We will also perform sensitivity analyses to evaluate the robustness of our results. For outcome data, we will not use imputation methods and will only exclude participants who do not have baseline data and at least one follow-up outcome measure.

### Sample Size

Our sample size has been calculated based on the primary outcome of the three Health Literacy Questionnaire (HLQ) domains. We assumed a minimal clinically important difference of 0.25 units in any one of the three HLQ domains. A sample size of 384 participants would result in greater than 90% power to detect a 0.25-unit change in an HLQ domain between the two arms, assuming an SD of 0.60, and at least 80% power, assuming an SD of 0.75. These SD values are based on published literature and equate to a standardized difference of 0.42 and 0.33, respectively; a standardized difference of 0.5 is considered a medium effect [33,34]. Our power calculation is based on conducting our analyses using 2-sided tests, a 5% significance level, and assuming 20% loss to follow-up (eg, due to death or kidney transplant).

For qualitative interviews, a maximum total sample size of 40 participants is planned. Interviews will continue until data saturation or until the maximum total sample size is reached.

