**Methods:**

We designed a multicenter pragmatic randomized controlled trial to compare the SUCCESS app plus usual care (intervention) to usual care alone (control). A total of 384 participants receiving in-center or home-based hemodialysis or peritoneal dialysis will be recruited from six local health districts in the Greater Sydney region, New South Wales, Australia. To avoid intervention contamination, a pragmatic randomization approach will be used for participants undergoing in-center dialysis, in which randomization will be based on the days they receive hemodialysis and by center (ie, Monday, Wednesday, and Friday or Tuesday, Thursday, and Saturday). Participants undergoing home-based dialysis will be individually randomized centrally using simple randomization and two stratification factors: language spoken at home and research site. Consenting participants will be invited to use the SUCCESS app for 12 months. The primary endpoints, which will be assessed after 3, 6, and 12 months of app usage, are health literacy skills, evaluated using the Health Literacy Questionnaire; decision self-efficacy, evaluated using the Decision Self-Efficacy Scale; and rates of unscheduled health encounters. Secondary outcomes include patient-reported outcomes (ie, quality of life, evaluated with the 5-level EQ-5D; knowledge; confidence; health behavior; and self-management) and clinical outcomes (ie, symptom burden, evaluated with the Palliative care Outcome Scale–Renal; nutritional status, evaluated with the Patient-Generated Subjective Global Assessment; and intradialytic weight gain). App engagement will be determined via app analytics. All analyses will be undertaken using an intention-to-treat approach comparing the intervention and usual care arms.

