**Primary outcomes: patient-reported outcomes**										
	Health literacy skills: the HLQ^e^, a multidimensional tool that measures health literacy across nine distinct conceptual domains, will be used. The median reliability of the HLQ domains is 0.88, with a range from 0.77 to 0.90 [26]. For the purpose of this study, we have selected three to domains to explore: Domain 2: have sufficient information to manage my health Domain 6: ability to actively engage with health care providers Domain 9: understand health information well enough to know what to do. Domain 2 assesses the strength of a participant’s agreement with the statement on a 4-point ordinal scale, ranging from 1 (“strongly disagree”) to 4 (“strongly agree”); domains 6 and 9 assess a participant’s perceived ease in task completion on a 5-point ordinal scale, ranging from 1 (“always difficult”) to 5 (“very easy”).	✓		✓		✓				✓
	Decision self-efficacy: the Decision Self-Efficacy Scale [23] measures self-confidence or belief in one’s ability to make decisions, including participation in shared decision-making. This item consists of 11 questions where participants rate their confidence engaging in decision-making behaviors, such as “Getting the facts about the medication choices available.” Items are rated on a 5-point ordinal scale ranging from 1 (“not at all confident”) to 5 (“very confident”).	✓		✓		✓				✓
	Rates of unscheduled health encounters: this includes unexpected hospital and emergency visits and unscheduled dialysis events in the past 3 months as reported by participants; this is also verified by extracting this information from electronic medical records.			✓		✓				✓

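### Five primary measures at three visits with no lead endpoint or timepoint, and a sample size built on any one of three HLQ domains at an unadjusted 5%

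*Protocol article*

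**What the plan says.** The abstract of the protocol article lists several primary endpoints measured at three visits: "The primary endpoints, which will be assessed after 3, 6, and 12 months of app usage, are health literacy skills", followed by decision self-efficacy and the rate of unscheduled encounters. The Study Outcomes section repeats the structure: "Our primary outcomes are health literacy, shared decision-making, and rates of unscheduled health encounters; these will be assessed at 3, 6, and 12 months". (It says shared decision-making where the abstract and Table 1 say decision self-efficacy; I count these as one measure.) Neither place gives one outcome or one visit precedence.

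Table 1 divides health literacy into HLQ domains 2, 6 and 9: "we have selected three to domains to explore". Domain 2 has a 4-point response scale and the other two a 5-point scale. No composite is defined. The primary set is therefore 3 + 1 + 1 = 5 measures.

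The Sample Size section treats the domains as the basis for N: "Our sample size has been calculated based on the primary outcome of the three Health Literacy Questionnaire (HLQ) domains". The effect is set by "We assumed a minimal clinically important difference of 0.25 units in any one of the three HLQ domains", and the power claim is "A sample size of 384 participants would result in greater than 90% power to detect a 0.25-unit change in an HLQ domain" at SD 0.60, with at least 80% at SD 0.75. The inputs are "conducting our analyses using 2-sided tests, a 5% significance level" and 20% loss to follow-up.

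The Data Analysis section gives regression models with study arm, a centre random effect and patient type. It states no ordering of the primary outcomes, no global test and no requirement that all of them succeed.

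**The concern.** A trial with several primary measures, several visits and no order among them can find its primary result in whichever measure and visit happens to be significant. Sizing the trial on a difference in any one of three domains, with the full 5% available to that domain, makes most sense if one positive domain is enough for a claim. On that footing the chance of at least one false-positive primary claim is well above 5%.

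The power statement is tied to the same choice. If the error rate is later controlled across the primary measures, the published power no longer describes the test applied to each domain. As the article stands, a reader cannot have both a trial-level 5% and the per-domain power quoted.

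**Working it through.** **Inputs from the protocol article.** N = 384, 1:1 allocation, 20% loss, difference 0.25, SD 0.60 or 0.75, two-sided 0.05. Analysed per arm: 384 × 0.8 / 2 = 153.6. The calculation treats patients as independent; clustering by dialysis-day group is a separate matter and is left out.

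**Step 1: reproduce the stated power.** Noncentrality = 0.25 / (SD × √(2/153.6)), on 305.2 degrees of freedom.
- SD 0.60: noncentrality 3.65, critical t 1.968, power 95.4%.
- SD 0.75: noncentrality 2.92, critical t 1.968, power 82.9%.

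Both stated bounds (above 90%, at least 80%) are met for one domain at 0.05.

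**Step 2: per-domain power at a Bonferroni level.** Same formula, with alpha divided by the family size.

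| Two-sided level | SD 0.60 | SD 0.75 |
|---|---|---|
| 0.05 (one domain) | 95.4% | 82.9% |
| 0.05/3 = 0.0167 (three domains) | 89.3% | 69.6% |
| 0.05/5 = 0.01 (five measures) | 85.4% | 62.9% |

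The first shortfall (89.3% against 90%) is marginal. The SD 0.75 shortfall is 80 − 69.6 = about 10 points at 0.05/3 and 80 − 62.9 = about 17 points at 0.01. Bonferroni ignores correlation and Holm rejects at least as often, so these are lower bounds for each family size.

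**Step 3: familywise error if any one result at 5% counts.** Under independence it is 1 − 0.95^k. The correlated figures come from simulated multivariate normal test statistics. The article gives no correlations, so these are assumed: 0.6 between HLQ domains, 0.4 between a domain and self-efficacy, 0.1 with encounters, and 0.5–0.8 across visits.

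| Family | Independent | Assumed correlations |
|---|---|---|
| Three domains, one visit (k = 3) | 14.3% | about 12% |
| Five measures, one visit (k = 5) | 22.6% | about 19–20% |
| Five measures, three visits (k = 15) | 53.7% | 43% (0.5 across visits), 39% (0.7), 35% (0.8) |

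With a common correlation between endpoints of 0.3–0.7 and 0.5–0.8 across visits, the ranges are 11–14%, 15–21% and 27–46%.

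**Step 4: power for at least one domain.** If all three domains move by 0.25 and each is tested at 0.05/3, the power to detect at least one, for between-domain correlations of 0.3, 0.6 and 0.8, is 99.2%, 97.7% and 95.7% at SD 0.60. At SD 0.75 it is 93.4%, 87.9% and 82.8%. If only one domain moves, power falls towards the per-domain figures in Step 2.

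**The case against.** The strongest reply is that the article does not say what a critic might read into it.

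- *Fifteen tests, each at 5%.* A reader might infer this, but no sentence states it. The outcomes are said to be assessed at three visits, and the 5% level appears only as a power input. The Missing Data section keeps participants with baseline and at least one follow-up measure, which also fits one longitudinal model per outcome. Fifteen is therefore an upper count, and 53.7% further assumes an independence that repeated visits on the same patients cannot have. This part of the reply stands. Three or five is the firm minimum.
- *Success in any one domain.* A reader might take this as the trial's success rule. The wording defines the difference used for power, and no success rule is stated. That stands too, so the error figures are conditional. But no stricter rule is given either.
- *Wrong power.* A reader might conclude that the power is miscalculated, or that both thresholds fail. It reproduces for one domain at 0.05. The thresholds fail only for per-domain power at an adjusted level, and at SD 0.60 with three domains only marginally. For at least one of three domains at 0.05/3 both hold if all three move (Step 4).
- *The analysis plan may deal with it.* A multiplicity rule may exist there, and its absence from an article is not the point. But the article itself fixes five unranked primary measures at three visits and a sample size at the full 5% for one domain. An adjustment made elsewhere would leave the published power describing a different test.

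It is also arguable whether literacy, self-efficacy and encounters form one error family. Even if only the three HLQ domains do, the error more than doubles.

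**Conclusion.** The point holds as a conditional one. If any one nominally significant primary result can support a claim, the familywise error is about 12–14% for three HLQ domains at one visit and about 19–23% for five measures at one visit. If each visit is tested separately, it is about 35–43%, with 53.7% as the independence figure. The lower end of each range rests on the assumed correlations.

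The published power is correct for a single domain at 0.05 but does not carry over to a controlled level. Per-domain power is then at least 89.3% and 69.6% over three domains, or 85.4% and 62.9% over five measures, for SD 0.60 and 0.75. Only the SD 0.75 loss is large. The defect is an unranked primary set combined with a power basis that leaves it unclear whether the 5% belongs to each domain or to the trial.

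**What to change.** Before outcomes are seen:

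1. Name one primary timepoint and make the other visits secondary. Twelve months, the end of the intervention period, is the natural choice.
2. Declare which measures are primary, and control the two-sided 5% familywise error over them at that timepoint with Holm or an equivalent prespecified procedure. A fixed hierarchy would also serve.
3. Restate per-domain power at the resulting level beside the unadjusted figure, keeping N at 384. For Holm over five measures the conservative first-step level is 0.01.

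The cost is wording in the protocol and analysis plan and a registry update, with no new data. The downside is lower stated power per endpoint. Keeping 80% at SD 0.75 after 20% loss would instead take about 473 participants at 0.05/3 or 528 at 0.01 (normal approximation, Bonferroni). Reporting the lower figure is the practical course with recruitment already under way.
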